### Exclusion criteria

triplets or higher order pregnancycriteria for EFM not met, including elective caesarean section prior to the onset of labour

### Planned interventions

The intervention is the decision-support software in this trial. In order to accurately reflect any potential impact of the decision-support software in contemporary NHS practice, such as changes in midwifery presence during labour consequent upon knowledge of the allocation, it is desirable that clinicians are not masked to allocation.

### Clinical management

The Guardian system will usually be used by all women in labour in the participating centres. It is only the decision-support software, which runs on this system, that is being tested in this trial.

The clinical management of women participating in this trial will remain unaltered by their participation, apart from the relatively uncommon circumstances when abnormalities of the CTG prompt the system in the ‘decision-support’ arm of the trial to issue a series of alerts or alarms, which will increase in urgency with the severity of the abnormality (See Fig. 2).

**Fig. 2 Fig2:**
[figure not shown]
Clinical Management flow diagram

Information about the trial will be provided to all women during the antenatal period, after their booking appointment. This process will be individualised for each participating centre depending on their routine practices. For example, in some centres, women will be provided with information about the trial at their routine ultrasound scan appointment (18–22 weeks). All women will have the opportunity to ask questions.

When a woman presents in early labour to the labour ward in a participating centre, she will be given a copy of the Participant Information Leaflet and a verbal explanation of the INFANT trial. She will then be asked whether she would like to participate in the study and if she agrees she would be asked to sign an INFANT trial consent form. If then at any point continuous electronic fetal monitoring (EFM) is commenced, then the midwife responsible for her care will check her eligibility to participate in the trial and check that the woman is still happy to take part and document this, then the woman will be randomised by the Guardian® system to either decision-support (intervention arm) or no decision-support (control arm).

All women admitted in labour to the participating centres will usually have their labour information recorded in the Guardian® system, according to the current practice in each centre. This does not change the way health professionals manage labour, it merely changes the way they manage the information generated by the process of monitoring labour and how they record this information. It will be clearly stated that women are free to withdraw from the study at any time for any reason without prejudice to future care, and with no obligation to give the reason for withdrawal.

Written informed consent will be obtained by means of a dated signature from the woman and the signature of the person who obtained informed consent; this would be the Principal Investigator (or a qualified health care professional with delegated authority). A copy of the signed informed consent document will be given to the women. A further copy will be retained in the woman’s medical notes, a copy will be retained by the Principal Investigator and a final copy will be sent to the Trial Coordinating Centre.

A senior investigator will be available at all times to discuss concerns raised by women or clinicians during the course of the trial.

### Outcome measures

The primary outcomes of this trial will be:

#### Short term

A composite of ‘poor neonatal outcome’ to include (a) all deaths *(intrapartum stillbirths plus neonatal deaths* i.e. *deaths up to 28 days after birth)* except deaths due to congenital anomalies, (b) significant morbidity: neonatal encephalopathy (moderate and severe); (c) admissions to the neonatal unit within 48 h of birth for ≥ 48 h with evidence of feeding difficulties, respiratory illness or encephalopathy where there is evidence of compromise at birth. (We recognise that the signs of mild encephalopathy can be subtle and hence a number of such babies are likely to have a range of non-specific signs such as respiratory difficulty and poor feeding rather than features more specifically associated with encephalopathy [27]. Hence including admission to the neonatal unit within 48 h of birth for equal to or greater than 48 h where there is evidence of compromise at birth. Since this is a mature group of babies, any difference in the incidence of these admissions is likely to result from differences in perinatal asphyxia).

*Note: the benefit of using a composite outcome is the increased incidence of the outcome; hence the sample size is reduced. The main problem occurs if the intervention affects different outcomes in different ways. In this trial, if the use of the decision-support software decreased deaths but increased significant morbidity there may be no difference in the short term primary outcome between the two arms of the trial, even though deaths were being prevented in one arm. The probability of this situation occurring appears very small. If decision-support prevents perinatal asphyxia it will have an effect on all the outcomes contained within the combined primary outcome.*

#### Long term

PARCA-R composite score [28, 29] at the age of 2 years for all infants with trial primary outcome and a further subset of 7000 babies.

*Note: Neurodevelopmental delay and cerebral palsy are the most important long-term adverse outcomes associated with perinatal asphyxia. However the incidence of moderate or severe cerebral palsy is of the order of 1.5–2.5/1000 live births, depending on the definition and the method of ascertainment. There is also uncertainty about the proportion of these cases that results from intrapartum asphyxia in mature infants; however, 30 % is a reasonable estimate3. Therefore, given the rarity of this outcome, it is unlikely that a clear difference could be demonstrated between the two groups with a trial of 46,000 births. So in order to have reassurance that any benefits of the intervention, with respect to short term outcomes, have not occurred at the expense of later neurodevelopmental delay,we will measure neurodevelopment in a proportion of the surviving children at the age of 2 years.*

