**Methods and design:**

An individually randomised controlled trial of 46,000 women who are judged to require continuous electronic fetal monitoring in labour.

*Eligibility criteria:* Women admitted to a participating labour ward who are judged to require continuous electronic fetal monitoring, have a singleton or twin pregnancy, are ≥ 35 weeks’ gestation, have no known gross fetal abnormality and are ≥ 16 years of age.

*Exclusion criteria:* Triplets or higher order pregnancy, elective caesarean section prior to the onset of labour, planned admission to NICU.

*Trial interventions:* Computerised interpretation of the CTG with decision-support.

Primary outcomes: *Short term:* A composite of ‘poor neonatal outcome’ including stillbirth after trial entry, early neonatal death except deaths due to congenital anomalies, significant morbidity: neonatal encephalopathy, admissions to the neonatal unit with 48 h for > 48 h with evidence of feeding difficulties, respiratory illness or encephalopathy where there is evidence of compromise at birth. *Long term:* Developmental assessment at the age of 2 years in a subset of 7000 surviving babies.

*Data Collection:* For all participating women and babies, labour variables and outcomes will be stored automatically and contemporaneously onto the Guardian® system.

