#### Secondary outcomes

Intrapartum stillbirth except deaths due to congenital anomaliesNeonatal deaths up to 28 days after birth except deaths due to congenital anomaliesModerate or severe encephalopathyAdmission to neonatal unit within 48 h of birth for ≥ 48 h with evidence of feeding difficulties, respiratory illness or encephalopathy (where there is evidence of compromise at birth)Admission to a higher level of careApgar score <4 at 5 minThe distribution of cord blood gas data for cord artery pHMetabolic acidosis (defined as cord artery pH <7.05 and base deficit in extracellular fluid ≥ 12 mmol/l)Resuscitation interventionsSeizuresDestination immediately after birthLength of hospital stay

Health and development outcomes at 24 months (for all infants with trial primary outcome and a further subset of 7000 babies):▪ Non-verbal Cognition Scale (PARCA-R)▪ Vocabulary Sub-scale (PARCA-R)▪ Vocabulary Sub-scale (PARCA-R)▪ Sentence Complexity Sub-scale (PARCA-R)▪ Late deaths up to 24 months (after the neonatal period)▪ Major disability and non-major disability at 2 years▪ Cerebral palsy▪ Breast feeding (collected at 12 and 24 months)

MaternalMode of deliveryOperative intervention (caesarean section and instrumental delivery) for (i) fetal indication, or (ii) failure to progress, or (iii) combination of fetal distress and failure to progress, or (iv) other reason.Grade of Caesarean sectionEpisiotomyAny episode of fetal blood samplingLength of (i) first stage, (ii) second stage and (iii) total length of labour from trial entryDestination immediately after birthAdmission to a higher level of care

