#### Data collection

For all participating women and babies, labour variables and outcomes will be stored automatically and contemporaneously onto the Guardian® system. Data collected via the system will be sent electronically to the trial co-ordinating centre at the UCL Clincial Trials Unit (UCL CTU) in London. Data will be extracted from the notes of babies admitted to the neonatal unit and for all neonatal deaths. It should be noted that not all data fields are collected at every centre. However, where an item is collected these data will be sent to the UCL CTU. The trial is not collecting the reason why continuous EFM is being used, as this is not recorded. All children surviving to be discharged home from hospital following their birth will be ‘flagged’ at the NHS Information Centre for those born in England and Scotland and all deaths occurring after discharge home from hospital will be notified to the trial co-ordinating centre at the UCL CTU. At 2 years after trial entry a sample of 7000 surviving children (3500 in each group) will be followed up at 2 years of age. This sample will be taken from within the sample recruited during the first 2 years of the project so that follow-up of this group can be completed around the time that the trial stops recruiting. As there seems little possibility that the nature of the effect of the intervention will vary over the duration of trial recruitment, this process will be the most efficient use of resources. For children in the follow-up group, their family will be sent a two part parent-completed questionnaire to assess the child’s health, development and well-being. The first part of the questionnaire comprises the PARCA-R, which has been previously validated as a means of assessing neurodevelopment in a trial setting. The second part focuses on general health issues, and has also been used previously [28, 29]. Major disability at 2 years will be assessed by questionnaires sent to the child’s parents and health care professionals. Major disability will be defined according to the criteria set out in the National Perinatal Epidemiology Unit (NPEU) and Oxford Regional Health Authority document and will include any major disability in the following domains: neuromotor function, seizures, auditory function, communication, visual function, cognitive function and other physical disability [30, 31].

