#### Effect size

The effect size which can be detected with 46,000 women (23,000 in each group), assuming a 5 % level of significance and 90 % power, is a 50 % reduction in poor neonatal outcome rate from 3 to 1.5 per 1000. We have approximated the number of women recruited with the number of infants born, even though women with a twin pregnancy are eligible to join the trial. Approximately 1 in 80 pregnancies are twin pregnancies, however, a proportion of these births will occur before 35 weeks’ gestation and a large proportion of the term births will be by elective caesarean section. We therefore estimate that fewer than 1 % of all births in the study will be twins. In a study of 164 preterm infants [29], the mean (SD) PARCA-R composite score at 2 years was 80 (SD 33) and the mean Mental Development Index (Bayley Scales of Infant Development II) was approximately half a standard deviation below the standardised mean of 100. If we assume that a normal group of term infants would have a PARCA-R composite score half a standard deviation above this sample of preterm infants, then we can estimate a mean (SD) 2 year score of 96 (SD33). Based on this estimate, a follow up sample of size 7000 (3500 per arm) in the INFANT study would have over 90 % power to detect a difference of 3 points in the PARCA-R component score with a two-sided 5 % significance level. The incidence of severe metabolic acidosis (cord-artery pH <7.05) is 10 per 1000 [36–39]. Our proposed sample size will therefore enable us to detect a 28 % relative risk reduction in incidence with over 80 % power in those babies who have their cord artery pH measured.

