#### Primary analysis

The primary analysis will be a comparison of women and babies allocated to “CTG with no decision support” with “CTG with decision support”. Participants will be analysed in the groups into which they were randomly allocated, regardless of allocation received. All women and babies with available data will be included, except for protocol violations and women randomised in error who did not give consent or who were under 16 years of age. The number (percentage) of babies with the composite primary outcome will be presented for each group, and the risk ratio plus 95 % confidence interval (CI) will be calculated. Risk ratios will be estimated using generalised estimating equations (GEE), or a similar method, adjusting for the stratification factors used in the randomisation (centre and singleton/twin pregnancy). This method of analysis will account for the correlation in outcomes between twins and siblings delivered in a subsequent pregnancy during the trial period. A log binomial model will be used in the first instance, but if convergence is not achieved then a log Poisson model will be used with a robust variance estimator [40]. The mean (SD) PARCA-R Composite score will be presented for each group, and the mean difference between groups plus 95 % CI will be calculated and compared using GEE (Gaussian model with identity link). For secondary outcomes including the components of the primary outcome, a 1 % level of statistical significance will be employed. Both adjusted and unadjusted estimates will be presented for all outcomes, but the primary inference will be based on the adjusted analysis.

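### The 2-year analysis set is defined in two ways; if the oversampled cases are pooled as the analysis section reads, the cerebral palsy comparison and all absolute rates are distorted

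*Protocol article*

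**What the plan says.** Two definitions of the 2-year set stand side by side.

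- **Cases plus 7000.** Under Outcome measures, Long term, the PARCA-R composite is measured "for all infants with trial primary outcome and a further subset of 7000 babies". The Secondary outcomes section repeats this: "Health and development outcomes at 24 months (for all infants with trial primary outcome and a further subset of 7000 babies". That list includes cerebral palsy, major and non-major disability, and late death.
- **7000 only.** The abstract has "Developmental assessment at the age of 2 years in a subset of 7000 surviving babies". Research methods also gives 7000 surviving children. Data collection says "a sample of 7000 surviving children (3500 in each group) will be followed up at 2 years of age", and adds: "This sample will be taken from within the sample recruited during the first 2 years of the project". The power statement under Effect size uses 7000, 3500 per arm.

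Primary analysis includes everyone with data, apart from protocol violations and certain women randomised in error. PARCA-R is summarised by mean and SD per group and "compared using GEE (Gaussian model with identity link". The stated adjustment is for centre and singleton/twin pregnancy. Sampling fractions and weights are not mentioned.

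**The concern.** Under the first definition, selection into the 2-year sample depends on the short-term primary outcome, which the intervention is meant to change. A case is certain to be followed up, while another infant has roughly a one in seven chance. An ordinary pooled comparison then counts cases several times too heavily, and in unequal numbers by arm if the intervention works. Part of the short-term result would reappear as a long-term result.

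This matters because the Long term section gives the purpose of follow-up as reassurance that a short-term gain has not been bought with later developmental harm. A distortion that favours decision support whenever the short-term outcome improves works against that purpose.

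Using only the further 7000 is no remedy if *further* means that cases are excluded, since the comparison is then restricted to infants without a post-randomisation outcome.

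**Working it through.** **The plan's own figure.** With 3500 per arm, SD 33 and a difference of 3 points, SE = 33 × √(2/3500) = 0.79. Then 3/0.79 − 1.96 = 1.84, so power is 96.7 %. This agrees with the stated power of over 90 %.

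**Inputs from the article.**
- Size: "46,000 women (23,000 in each group".
- Effect: "reduction in poor neonatal outcome rate from 3 to 1.5 per 1000", that is 69 v 34.5 cases.
- Deaths: 0.35 + 0.70 = 1.05 per 1000, so (3 − 1.05)/3 = 65 % of cases survive. I assume the same share in both arms.
- Surviving cases: 69 × 0.65 = 44.9 and 34.5 × 0.65 = 22.4.
- Non-cases followed up: taken as 3500 per arm.

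**Sampling fraction.** 7000/46,000 = 15.2 %, a weight of 6.6. The 7000 come from the first 2 years only. With even accrual over 36 months that window holds 46,000 × 2/3 = 30,667, so the fraction within it is 22.8 % and the weight 4.4.

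**Share of cases in the set.** Unweighted: 44.9/3544.9 = 1.27 % v 22.4/3522.4 = 0.64 %. Among all survivors: 0.195 % v 0.098 %.

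**Cerebral palsy, route 1.** Assume 25 % risk in surviving cases (the background figure for moderate encephalopathy, applied here to all cases) and 1.5 per 1000 in non-cases.
- Full cohort: 1.98 v 1.74 per 1000, RR 0.88.
- Pooled, control: (44.9 × 0.25 + 3500 × 0.0015)/3544.9 = 4.64 per 1000.
- Pooled, intervention: (22.4 × 0.25 + 3500 × 0.0015)/3522.4 = 3.08 per 1000. RR 0.66.
- Over 15–35 % in cases and 1–2 per 1000 in non-cases, a true RR of 0.80–0.94 becomes 0.59–0.76.

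**Cerebral palsy, route 2.** Use the Long term section's incidence (1.5–2.5 per 1000; 2 taken here) and its 30 % share due to intrapartum asphyxia. Assume that this share falls wholly among cases and is halved by the intervention.
- Full cohort: RR = 0.70 + 0.30 × 0.5 = 0.85; control rate 2.0 per 1000.
- Pooled, control: (13.8 + 4.9)/3544.9 = 5.3 per 1000.
- Pooled, intervention: (6.9 + 4.9)/3522.4 = 3.35 per 1000. RR 0.635.
- With a share of 20 %, RR 0.90 becomes 0.69; with 10 %, 0.95 becomes 0.79. These ratios are the same at 1.5, 2 and 2.5 per 1000.

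**Can it hide harm?** Take route 1, but assume that risk in intervention-arm non-cases rises from 1.5 to 1.9 per 1000. The full-cohort RR is 1.08; the pooled RR is (5.6 + 6.65)/3522.4 over 4.64 per 1000, about 0.75.

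**Major disability** (prevalence not given, so assumed; share of it among cases in brackets).
- 1 % (5–10 %): RR 0.975–0.95 becomes 0.88–0.79.
- 3 % (2–4 %): 0.99–0.98 becomes 0.95–0.90.
- 5 % (1–2 %): 0.995–0.99 becomes 0.975–0.95.

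**PARCA-R.** Assume that cases score 33 points (1 SD) lower. The pooled arm difference is 33 × (1.27 % − 0.64 %) = 0.21; the full-cohort value is 33 × (0.195 % − 0.098 %) = 0.03. The bias is 0.18 points, or 0.22 SE. It is 0.09–0.35 for deficits of 16.5–66 points, and at most 0.53 if every case survived.

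**Equal arms.** With equal case rates and equal risks within strata, every pooled comparison is unbiased. Only the absolute levels move.

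**The case against.** A reader might infer that the plan specifies an unweighted comparison. It does not say so. A Gaussian GEE can carry weights, and weights or a restricted analysis population may be set in an analysis plan that is not shown. The Health economics section also gives a separate reason to follow every surviving case, so the extra cases may never have been meant for the randomised comparison. The power statement, built on 7000, fits that reading. This stands as far as intent goes. It does not remove the conflict between the two definitions. Nor does it change what Primary analysis says if followed literally: everyone with data, plain group means, and adjustment for two factors.

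A reader might also infer that the PARCA-R primary comparison is seriously biased. The arithmetic does not support this: a sixfold inflation of 0.03 points is still about 0.2 points. The same caution applies to disability, where the size depends on a prevalence that the article does not give.

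Finally, cerebral palsy is a secondary outcome tested at the 1 % level, and the article itself doubts that a clear difference could be shown. Route 1 implies about 16 v 11 affected children, z about 1.05, so even the distorted contrast would not be expected to reach significance. This stands too, but the reported estimate and rates would still be wrong.

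**Conclusion.** The point holds as an inconsistency in the analysis set of a primary outcome, joined to a stated estimator that does not suit one of the two stated samples. It should be fixed before analysis, chiefly for cerebral palsy and for absolute rates. The cerebral palsy figures (RR about 0.85–0.88 becoming about 0.635–0.66, control rate about 2 becoming about 5 per 1000) depend on four things: all cases being pooled without correction, the planned halving of the primary outcome, 65 % survival of cases, and the assumed concentration of cerebral palsy among cases. For major disability the distortion is slight to moderate; for PARCA-R it is small and does not threaten the comparison at the planning rates.

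**What to change.** State one 2-year analysis set in every section that describes it, and match the analysis to it. Either of two routes works.

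- **(a) Simple random sample.** Draw 7000 survivors by arm regardless of case status and base the long-term comparison on them, with cases present only as drawn. Describe the additional cases separately and use them for the economic model. At the planning rates the draw would contain only about 3500 × 0.195 % = 7 and 3500 × 0.098 % = 3 cases, so it says little about cerebral palsy.
- **(b) Two-phase sample.** Analyse all cases plus the 7000 non-cases with inverse sampling-probability weights by arm and robust standard errors, for PARCA-R and every 24-month outcome. Cases and non-cases must refer to the same recruitment period. Either restrict cases to the first-2-years window (non-case weight about 4.4 under even accrual), or weight non-cases up to the whole trial (about 6.6). The second choice relies on the Data collection section's assumption that the effect does not vary over recruitment. Mixing cases from 36 months with a weight of 4.4 would leave cases over-represented by 36/24 = 1.5 times.

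The cost is a change of wording, weights that are known from the design, and under (b) a small loss of precision.

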### The problem of perinatal asphyxia

Perinatal asphyxia, if severe, can result in intrapartum stillbirth. If less severe it results in the development of an encephalopathic state in the newborn. This is characterised by a decreased level of consciousness, altered reflexes and abnormal tone and ultimately permanent damage to the brain. Moderate or severe neonatal encephalopathy occurs in approximately 2/1000 births [1]. With more severe asphyxial encephalopathy there is an increasing risk of death or neurodevelopmental abnormalities: up to 30 % of affected neonates will develop seizures and approximately 25 % of infants who have moderate asphyxial encephalopathy will develop cerebral palsy. Almost all infants with severe encephalopathy die or survive with multiple handicaps [2]. Perinatal asphyxia may account for up to 30 % of cases of cerebral palsy [3] and it is a very significant health-care and financial burden on the NHS. A reduction in the number of babies born with perinatal asphyxia would reduce the associated mortality and, amongst survivors, the burden of ill health and incapacity. It could also result in substantial savings in litigation costs in the UK.

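### At 2 years, cerebral palsy and major disability are compared among survivors only, with no death-or-disability outcome beside them

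*Protocol article*

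**What the plan says.** Under Outcome measures, Long term, the protocol article explains that cerebral palsy is too rare to show a clear difference, so "we will measure neurodevelopment in a proportion of the surviving children at the age of 2 years". The purpose is reassurance that short-term benefits "have not occurred at the expense of later neurodevelopmental delay". The PARCA-R composite is the long-term primary outcome, to be obtained "for all infants with trial primary outcome and a further subset of 7000 babies". Data collection describes the sample again: "a sample of 7000 surviving children (3500 in each group) will be followed up at 2 years of age".

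Under Secondary outcomes, "Major disability and non-major disability at 2 years" is one entry and cerebral palsy another. Intrapartum stillbirth, neonatal death and death between the neonatal period and 24 months are further separate entries. No entry counts death together with disability.

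Primary analysis compares groups as allocated, takes the PARCA-R mean difference between groups, and sets a 1% significance level for secondary outcomes. It does not say how deaths enter the 2-year comparison.

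The Short term section does consider a trade between death and morbidity: "if the use of the decision-support software decreased deaths but increased significant morbidity there may be no difference in the short term primary outcome". It judges this very improbable and discusses it only for the short-term composite.

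**The concern.** The intervention is intended to prevent deaths, so survival to 2 years is itself affected by allocation. A comparison restricted to survivors then sets unlike groups side by side: the decision-support arm would include babies whose counterparts in the control arm died. The protocol's own background section makes this plausible: "Almost all infants with severe encephalopathy die or survive with multiple handicaps".

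The question put to the 2-year data is whether benefit came at a developmental cost. A higher cerebral palsy or disability rate among survivors could mean that the software caused impairment, or that it kept alive babies who would have died. These readings support very different conclusions, and the survivors-only rate gives no help in choosing between them.

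The follow-up design sharpens this. A rescued baby who meets the primary outcome is followed with certainty, while other children are followed only if sampled.

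**Working it through.** **Inputs from the protocol article.** 23,000 women per arm, taken as births (Effect size). Intrapartum stillbirth 0.35 and neonatal death 0.7 per 1000. Primary outcome 3 per 1000 in controls, with a 50% reduction as design effect. Cerebral palsy 1.5 to 2.5 per 1000 (Long term). PARCA-R mean 96, SD 33, 3,500 per arm, difference 3 points (Effect size).

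**The plan's own figure.** Power for 3 points with SD 33 and 3,500 per arm at two-sided 5% is 96.7%, which agrees with the stated power of over 90%. The standard error is 33 × √(2/3500) = 0.79.

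**Deaths and follow-up set, per arm.**
- Deaths in controls: 23,000 × 1.05/1000 = 24.2. Halved: 12.1.
- Primary-outcome infants in controls: 23,000 × 3/1000 = 69, of whom 69 − 24 = 45 survive.
- Followed in controls: 3,500 + 45 = 3,545.
- A random 3,500 would contain only 12.1 × 3,500/23,000 = 1.8 of the averted deaths. Full follow-up of primary-outcome infants brings in all 12.

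**Scenario.** Deaths are halved, all 12 averted deaths survive impaired and meet the primary outcome, other morbidity is unchanged, and nobody is lost.

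*Cerebral palsy, unweighted.* Control cases are 3,500 × background, and decision-support adds 12.1. P values are from a pooled two-proportion z test.

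| Background per 1000 | Cases, control v decision-support | Risk ratio | p |
|---|---|---|---|
| 1.5 | 5.2 v 17.3 | 3.29 | 0.011 |
| 2.0 | 7.0 v 19.1 | 2.72 | 0.018 |
| 2.5 | 8.8 v 20.8 | 2.37 | 0.027 |

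Adding an assumed 8 cases per arm from the other surviving primary-outcome infants gives ratios of 1.90, 1.80 and 1.72 (p 0.053 to 0.075). The range is therefore roughly 1.7 to 3.3, and no value reaches 1%.

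*Major disability.* The protocol gives no background rate. Assuming 1%, 2% and 5%, the ratios are 1.34, 1.17 and 1.06 (p 0.19, 0.34 and 0.54).

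*PARCA-R.* Even if every added survivor scored 0, the mean would fall by 12.1 × 96/3,557 = 0.33 points. About 1.55 points are needed for p < 0.05.

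**Effect of weighting.** Each sampled child stands for (23,000 − 69)/3,500 = 6.55 babies. At 2 per 1000 the 7 control cases represent 7 × 6.55 = 46, and the weighted ratio is (46 + 12)/46 = 1.26. At 1.5 and 2.5 per 1000 it is (34.4 + 12.1)/34.4 = 1.35 and (57.3 + 12.1)/57.3 = 1.21. Weighting shrinks the lean towards harm but does not remove it.

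**Counting deaths as well (weighted, 2 per 1000).** Death or cerebral palsy is 24 + 46 = 70 v 12 + 58 = 70, no difference. If only half of the averted deaths survive impaired, cerebral palsy alone is 46 v 52 (ratio 1.13, towards harm), while death or cerebral palsy is 70 v 12 + 52 = 64 (ratio 0.91, towards benefit). The two summaries then point in opposite directions.

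**The case against.** The strongest objection is that the scenario is extreme. It needs every averted death to survive impaired and no fall in other morbidity. The short-term composite would then be 24 + 45 = 69 v 12 + 57 = 69, a null result rather than the planned halving. The Short term section expects asphyxia prevention to act on all components. This stands: the ratios above are upper-end illustrations for 12 averted deaths. The direction of the distortion does not depend on full conversion, as the half-conversion case shows.

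Second, deaths are not hidden. Each kind of death is a listed outcome, all primary-outcome infants are targeted for follow-up, and the health economics section plans a cost per disability-free life year. A reader might infer from the separate listing that death and disability cannot be combined. The documents do not support that; they can be, but the denominators differ and no combination is named.

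Third, a composite cannot separate new impairment from rescue either: equal totals also fit 12 healthy rescues plus 12 newly disabled children. Used alone, it could let fewer deaths mask more disability. This stands, and it is why the composite belongs beside the separate components and should not replace them.

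Fourth, the statistical analysis plan is not shown and may deal with deaths at 2 years. That is possible, but the protocol sets out the outcome list, and a combined outcome is not on it.

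**Conclusion.** The point holds for cerebral palsy and major disability. Both are compared among survivors, no outcome joins them to death, and a survival difference between arms can push the estimates towards harm when death-or-disability is unchanged or improved. With deaths halved and all 12 averted deaths impaired, the unweighted cerebral palsy ratio is roughly 1.7 to 3.3 and the major disability ratio about 1.06 to 1.34. None reaches the 1% level, so the risk is a misleading estimate more than a false significant result. Only if all 24 expected deaths became impaired survivors, well beyond the design effect, would cerebral palsy pass 1%; major disability still would not (lowest p 0.014).

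Two stronger readings are not supported. A reader might infer that PARCA-R would also look like harm, but it moves by at most 0.33 points (0.65 if all 24 deaths converted), against a standard error of about 0.79 and a design difference of 3. A reader might also compare disability only among surviving primary-outcome infants, where a 25% background gives 11 of 45 v 23 of 57, a ratio of 1.6. That subset is defined after randomisation and is not a comparison the protocol plans.

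The figures assume equal arms, complete follow-up, the protocol's event rates, and assumed values for background disability and for the 8 further cerebral palsy cases. This is an inexpensive improvement to the outcome list and leaves the long-term primary outcome sound.

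**What to change.** Add to Secondary outcomes: *death (excluding congenital anomaly) or major disability at 2 years, by allocation*. Base it on all randomised babies in the follow-up frame, including those who died before selection. Weight for the sampling, so that deaths and primary-outcome infants, taken in full, are set correctly against the sampled remainder.

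Report it beside the separate death, disability, cerebral palsy and PARCA-R results when making the reassurance statement in the Long term section, and do not let it stand in for them.

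The frame needs a sentence of definition. The 7000 come from the first 2 years of recruitment, whereas deaths and primary-outcome infants arise throughout. Weights over the whole trial therefore rely on the protocol's view that the effect does not vary during recruitment.

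The cost is one outcome line and one weighted analysis on deaths and questionnaires already planned. The downside is one more secondary outcome, which may be driven by deaths if disability is rare.
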